# Cognitive-behavioral family therapy as psychoeducation for adolescents with high-functioning autism spectrum disorders: Aware and Care for my Autistic Traits (ACAT) program study protocol for a pragmatic multisite randomized controlled trial

**DOI:** 10.1186/s13063-020-04750-z

**Published:** 2020-09-29

**Keywords:** High-functioning autism spectrum disorder, Randomized controlled trial, Cognitive-behavioral family therapy, Psychoeducation

## Abstract

**Background:**

One aim of an autism spectrum disorder (ASD) diagnosis is to obtain special support for the disorder, though this does not guarantee practical support. We developed a psychoeducational program using cognitive-behavioral therapy (CBT) and Aware and Care for my Autistic Traits (ACAT) for Japanese adolescents with high-functioning ASD and their parents.

**Methods:**

This multisite study is a randomized controlled trial. In total, 24 participants will be assigned to the ACAT group and 24 to the treatment-as-usual (TAU) group. The ACAT group will receive a weekly 100-min session for 6 weeks, regular medical care, and one follow-up session. In this ongoing clinical trial, we will compare the scores of the measures recorded in the pre- and post-intervention stages between the ACAT and TAU groups. A total of 41 patients out of a target of 48 have participated in the trial to date. The primary outcome measure is the Autism Knowledge Questionnaire. Secondary outcome measures include Barriers to Access to Care Evaluation 3rd Edition, the Strengths and Difficulties Questionnaire, the Vineland Adaptive Behavior Scales second edition, the Parenting Resilience Elements Questionnaire, the General Health Questionnaire 12, and the Depression Self-Rating Scale for Children assessments, as well as an electroencephalographic recording.

**Discussion:**

It is expected that participants in the ACAT group will significantly increase their self-understanding and awareness of ASD symptoms compared to those in the TAU group. Additionally, the ACAT group is expected to exhibit improved social adaptation and mental health if children and parents are able to better understand the ASD characteristics through sessions. This intervention will contribute to the establishment of an effective evidence-based treatment strategy for adolescents with ASD.

**Trial registration:**

UMIN Register 000029851. Registered on January 06, 2018

## Background

Autism spectrum disorder (ASD) is a pervasive neurodevelopmental disorder characterized by impairments in social communication and restricted, repetitive patterns of behavior, interests, or activities [1]. ASD is a relatively common neurodevelopmental condition that affects 1–1.5% of the population [2, 3]. Individuals with high-functioning ASD (HF-ASD) have normal-range IQs and extensive verbal abilities and usually attend regular schools. Nevertheless, their difficulties are potentially serious and can include impaired social relations, obsessions, and uneven levels of intellectual and cognitive functioning [4]. When patients with HF-ASD become independent and increase social interactions as they enter adolescence, they become aware of their differences to their surroundings, which tends to lower their self-efficacy and self-esteem and increase feelings of depression and anxiety [5–7].

An extensive treatment has recently been made available to support the central characteristics of ASD early in life, as evidenced by the Early Start Denver Model [8] and parent-mediated communication-focused treatment in children with autism (PACT) [9]. These treatment programs are not available for people with autism post-early childhood. However, individuals with autism who are diagnosed later may experience benefits in social functioning by gaining support, such as social skills training [10, 11] and/or reasonable accommodation [12].

In childhood and adolescence, individuals without knowledge of focal features and those with HF-ASD can easily experience self-stigma such as feeling “abnormal” or “inferior” [13]. As stigma acts as a barrier to help-seeking behavior [14], patients may experience reduced opportunities to obtain support alongside increased feelings of experiencing difficulties [15].

Conversely, the provision of psychoeducation on ASD has been reported to decrease adverse feelings toward children with the disorder. Gaining knowledge on ASD is also extremely important to the parents. Farrugia reported that parents who gained medical knowledge about ASD experienced decreased stigma toward children with ASD [16]. In addition, Gordon et al. [17] demonstrated that participation in a brief parent-child program of psychoeducation, the PsychoEducational Groups for Autism Spectrum Understanding and Support (PEGASUS), which sought to promote self-understanding and acceptance of HF-ASD, increased self-awareness in both parents and children. The PEGASUS is a psychoeducation group for young individuals with HF-ASD and their parents that promotes awareness of autistic traits. However, it cannot help them cope with behavioral problems in multiple domains. Therefore, we conjectured that cognitive-behavioral family therapy (family CBT) may help HF-ASD children/adolescents and their families to understand the central characteristics of ASD and cope with the cognitive and behavioral problems caused by autistic traits. The CBT treatment seeks to produce cognitive alterations in various ways to endure emotional and behavioral changes [18]. Reports have suggested that the application of CBT for ASD represents a major advance in the treatment of co-occurring anxiety and depression in HF-ASD patients [6, 19, 20]. There is a small body of literature indicating that CBT is effective for managing problems faced by young individuals with ASD, such as anger, anxiety, social interaction, and emotional understanding [21]. For children with ASD, modifying the standard CBT protocol is necessary to induce general and permanent changes [22]. In this regard, we have included family participation because the parents need to understand the distinct features of their children’s AD to understand the considerations required when caring for them.

For this study, the authors developed a new intervention for HF-ASD children/adolescents termed the Aware and Care for my Autistic Traits (ACAT) program. This program includes psychoeducation and family CBT for HF-ASD children/adolescents and their parents/guardians. The details of this program are explained in the “Methods/design” section.

Since the ACAT program is based on psychoeducation that augments family CBT, the primary outcome is the increased awareness of ASD measured by the child/youth version of the Autism Knowledge Quiz (AKQ) [17]. In addition, a social adaptation scale and a stigma scale are collected as secondary outcomes to monitor the relative improvement of these two factors. Moreover, investigating the relationship between behavioral and neural changes after the intervention can provide strong evidence that the intervention has an impact on behavioral and neural substrates. Therefore, we will record resting-state electroencephalograms (EEG) as a neural outcome in this study for exploratory purposes. Although the causes and biomarkers of ASD remain unclear, evidence suggests that ASD is a neurobiological disorder underscored by abnormal brain activity related to the observed social deficits [23]. EEG, which primarily measures neurophysiological changes related to postsynaptic activity over the cortex, can capture and characterize abnormal brain activity. For example, individuals with ASD showed increased short-range connections in the lateral-frontal electrodes and decreased long-range connections in the fronto-occipital electrodes compared with healthy individuals [24]. Moreover, other studies have shown that altered EEG patterns are normalized in response to improved social behaviors after social training programs, which indicates that psychosocial interventions have the potential to alter brain activity as measured by EEG.

### Objectives

This study aims to examine the efficacy of the newly developed psychoeducation program for parents and individuals with HF-ASD, or ACAT, by comparing with the treatment-as-usual (TAU) group. Individuals and parents who are assigned to the ACAT group will keep their current treatments, which the ACAT program will augment. We hypothesize that the ACAT group will show greater children and parents’/guardians’ understanding and awareness of their autistic attributes than the TAU group. Randomized controlled trials will be conducted at multiple sites to investigate the relative efficacy of ACAT compared to TAU.

Our goal is to examine the relative efficacy of the combination of psychoeducation and family CBT for both child/adolescent patients with HF-ASD and their parents/guardians after diagnosis. This study will help to establish a new evidence-based psychoeducational treatment strategy for child/adolescent patients with HF-ASD and their parents/guardians. It will enable more treatment options as an after-diagnosis service and improve the dissemination of psychoeducation and CBT for HF-ASD.

## Methods/design

### Study design

This study is designed as a prospective randomized open-label endpoint trial with two parallel intervention groups consisting of a 6-week treatment of treatment-as-usual (TAU group) alone and an ACAT combined with TAU (ACAT group). It is randomized, multisite, stratified, single-blinded, and is conducted through a parallel between-group design.

Qualified individuals who consent to this trial are randomly assigned to a TAU sustained group or a COMB group that combines psychoeducation and family CBT. The study is planned in accordance with the Standard and Protocol Items: Recommendations for Interventional Trials [25] and will be analyzed and reported in line with the Consolidated Standards of Reporting Trials Recommendations [26].

### Participants

The eligible participants in the current study are individuals diagnosed with ASD and their parents or guardians. Before the final inclusion, both written and verbal informed consent is obtained from all participants in the study.

#### Inclusion criteria

The participants in this study comprise patients and their parents/guardians who meet the following criteria during the screening process:

*Individual child/adolescent with ASD:*
Meet the cutoff value for ASD measured using the Autism Diagnostic Observation Schedule [27] or Autism Diagnostic Interview-Revised [28]Have a verbal IQ of 90 or above as measured by the Wechsler Intelligence Scale for Children [29]Have a social difficulty assessment of “some need” or higher measured by the Strengths and Difficulties Questionnaires [30]Aged between 10 and 17 years at the time of consent, with one of the parents being eligible to participate in psychoeducation and CBT (if assigned to COMB)Diagnosed with ASD by a primary doctor or other doctors or rehabilitation center for childrenReceived outpatient psychiatric careAble to understand CBT and is mentally and physically able to sustain therapy for at least 2 months

*Parents/guardians of ASD individuals:*
Living with the ASD individual as a parent or a grandparent and acts as a guardianAble to participate in CBT once a week with the ASD individual

#### Exclusion criteria

*Individual child/adolescent with ASD:*
Current active suicidal intentActive repetitive antisocial behaviorActive severe degenerative physical disorder that may disrupt CBT

*Parents/guardians of ASD individuals:*
Must not meet the diagnostic criteria for psychiatric disorders measured by the Mini-International Neuropsychiatric Interview [31] to be eligible for participation in the studyUnable to accompany the patient to the sessions

### Procedures

Beginning in March 2018, recruitment, treatment, and data collection are being conducted in two cities in Japan (Chiba and Fukushima). The last follow-up treatment will be completed in August 2020. Children and adolescent outpatients (10–17 years of age) diagnosed with ASD and their parents and guardians are informed about the intervention in waiting rooms at Chiba University Hospital and a local psychiatry clinic. For those who show interest, more information is provided by the recruitment staff.

The flow chart of this clinical trial is shown in Fig. 1. The trial will be conducted over 6 weeks of interventions and 4 weeks of follow-up. To evaluate treatment efficacy and safety, outcome measure assessments will be administered before and after the interventions. The participants assigned to COMB will continue their usual treatment with their primary doctors and also participate in six sessions of the ACAT program (a 100-min psychoeducation and family CBT program developed by the authors) every week (the ACAT program is conducted for a duration of 6 weeks). Participants taking psychotropic drugs regularly as medical treatment will be requested to remain on stable dosage during the interventions; however, the dosage may change if their primary or prescribing physicians consider it medically necessary. Any change in the dosage will be recorded in the list of daily doses of psychoactive drugs. A follow-up interview will be conducted 4 weeks after the completion of the interventions (10th week). Interviews and symptom assessments will be undertaken at each facility during week 0 (pre-intervention), week 6 (post-intervention), and week 10 (follow-up). The participants assigned to the TAU group will be required to continue their usual treatment with their primary doctors. Furthermore, a combination of the following treatments is prohibited with their usual treatment: psychotherapy that conforms to CBT or physiological therapies, including electroconvulsive therapy and magnetic stimulation therapy. The interviews and symptom assessments at pre-intervention, post-intervention, and follow-up will be conducted for TAU at each facility in the same manner as that for COMB. The restrictions for psychotropic drugs are the same as those for the COMB group. All sessions and psychological examinations are free for the participant. Both child/adolescent patients and their parents/guardians will receive 10,000 yen (about 100 USD) after completion of the last measurement. Any harm that occurs will be reported after the study period, whether or not it could have been related to the study treatment. Patients will be observed for up to 4 weeks (after discontinuation). To date, 41 patients in total have been randomized.

**Fig. 1 Fig1:**
[figure not shown]
CONSORT flow chart of the clinical trial

### Randomization and blinding

Enrollment and randomization are based on the central registration system of the Clinical Research Data Center at Chiba University Hospital, Chiba, Japan. Two allocation factors are used for stratification: the degree of knowledge (high or low) regarding the characteristics of ASD according to the primary outcome measure, the Autism Knowledge Quiz-Child (AKQ-C), and gender (male or female). At the end of the baseline assessment, eligible participants will be randomly assigned to either the TAU arm or ACAT plus TAU arm at a ratio of 1:1, with assignments made using the minimization method, ensuring a balance across baseline AKQ scores and gender. Each participant will then be assigned to one of the two treatments. Participants will not be blinded to the group to which they are assigned before consenting to participate in the study. However, trained testers, who will assess all outcome measures except the self-assessment scale, will be blinded to the group.

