### Sample size

The sample size was calculated using the G*power software version 3.1.9.2 with a power of 0.80 and *α* = 0.05 (two-tailed). In a previous study [17], the change in AKQ’s “ASD awareness” was 2.26, and the effect size was 0.92. Considering a drop out ratio of 20%, the ideal sample size was estimated as 48.

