### Statistical methods

#### Statistical analysis plan

We are currently collecting data from 41 of 48 child/adolescent ASD patients and their parents/guardians. Treatments will end during the spring of 2020, and analysis of the data will commence in the summer of 2020. The purpose of this study is to examine the relative efficacy of ACAT for child/adolescent ASD patients and their parents/guardians, in terms of ASD awareness scores, compared to the TAU group. Therefore, the primary analysis will evaluate the differences in score variations (i.e., the ACAT and TAU groups’ mean variations) for ASD awareness from week 0 (baseline) to week 6. Relative efficacy will be indicated when the point estimate of mean variation difference has a positive value and when the value of the ACAT group statistically exceeds that of the TAU group. The examination of scores will be based on an analysis of covariance (ANCOVA) for interval estimation of mean variation differences and calculation of the P value using allocation factors as adjustment factors (gender and AKQ-C score). The secondary evaluation of efficacy items will supplement the main results of the analysis, and redundancy will not be adjusted. The level of significance for the hypothesis test is 5% on two sides, with a two-sided confidence interval of 95%.

The results of the BACE-3, AKQ-P, SDQ, Vineland-2, DSRS-C, PREQ, and GHQ-12 (self-completed by parents) will be analyzed using the same techniques used for the assessment of the main evaluation items. In addition, EEG of individuals with HF-ASD as well as their parents/guardians will be recorded at pre-intervention, post-intervention, and follow-up to investigate neurological changes. EEG signals will be registered with a 19-channel box of Mitsar-EEG 201 (Mitsar Co. Ltd.). The 19-channel EEG cap will be fitted in accordance with a standard 10–20 system. EEG analysis will be conducted based on graph theory. The overall efficiency, clustering coefficients, connection between the left and right hemispheres, and network resilience will be calculated and compared between the ACAT and TAU groups.

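### Site is neither a minimization factor nor an ANCOVA covariate in this two-city trial; adding it to the model is a cheap, minor gain in precision and in protection against chance imbalance

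*Protocol article*

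**What the plan says.** The Study design section describes the trial as multisite. The Procedures section says "recruitment, treatment, and data collection are being conducted in two cities in Japan (Chiba and Fukushima"), names a university hospital and a local psychiatry clinic as places where families are approached, and has interviews and symptom assessments done at each facility.

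Randomization and blinding states that "Two allocation factors are used for stratification". These are AKQ-C knowledge (high or low) and gender, balanced by minimization through a central registration system.

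The Statistical analysis plan section specifies an ANCOVA of the week 0 to week 6 change in awareness, "using allocation factors as adjustment factors (gender and AKQ-C score"). Secondary scales are to be analysed with the same techniques. No section names site, city or facility as an allocation factor, covariate or random effect.

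**The concern.** Both lists are given as complete, and the second is defined by the first. The article therefore fixes a model without site; it does not leave the matter to a fuller document.

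Site could plausibly matter here. The primary endpoint is the structured-interview section of the AKQ-C, given locally by trained testers. Usual care, which is the whole comparator, comes from participants' own doctors. A university hospital and a local clinic may also see different families.

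If change in awareness differs by site, two connected things follow. Variation between sites stays in the residual and widens the confidence interval. And if the arms happen to be split unevenly across sites in the trial as run, part of the site difference sits in the observed treatment difference with nothing in the model to remove it.

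**Working it through.** **Inputs from the article.** Two-sided 5% ("The level of significance for the hypothesis test is 5% on two sides"), power ("with a power of 0.80"), effect ("the effect size was 0.92"), dropout ("Considering a drop out ratio of 20"%), total ("the ideal sample size was estimated as 48"), 24 per arm, two cities.

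**Inputs assumed, because the article gives none.** Two sites, one per city; smaller site with m = 6, 12, 16 or 24 of 48; site difference in awareness change ds = 0, 0.2, 0.5 or 0.8 SD; total SD held at 1.

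**1. The plan's own figure.** The normal approximation for d = 0.92 gives 19 per arm, 38 in total; 38/0.8 = 47.5, so 48. The t-test gives 20 per arm, 40 in total; 40 × 1.2 = 48 (40/0.8 would be 50). The stated 48 is reproduced.

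**2. Chance imbalance in site share.** If allocation ignores site, the number X of the m smaller-site participants who fall in one arm of 24 is hypergeometric. The between-arm difference in site share is (2X − m)/24, with SD = (2/24) × √[m × ¼ × (48 − m)/47]. The typical shift in the estimate is ds × SD, shown for ds = 0.5. The between-site share of total variance is p(1 − p) × ds², with p = m/48.

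| m | SD of difference | P(25 points or more) | Typical shift, ds = 0.5 | Between-site variance, ds = 0.5 |
|---|---|---|---|---|
| 6 | 0.097 | 0.022 | 0.048 SD | 0.027 |
| 12 | 0.126 | 0.093 | 0.063 SD | 0.047 |
| 16 | 0.138 | 0.125 | 0.069 SD | 0.056 |
| 24 | 0.146 | 0.148 | 0.073 SD | 0.0625 |

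For m = 6, a 25-point difference needs all six in one arm: 2 × C(24,6)/C(48,6) = 0.022. Simulated minimization on two other factors (biased coin 0.8, N = 48) gave imbalance SDs of about 0.13 to 0.15 for site splits of 70/30 and 50/50, so the hypergeometric figures are a fair guide.

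**3. Shift at a 25-point imbalance.** 0.5 × 0.25 = 0.125 SD; 0.125/0.92 = 13.6% of the planned effect. The standard error at N = 48 is about 2/√48 = 0.29 SD, so this is 0.125/0.29 = 0.43 standard errors. The typical shift is 0.048/0.92 = 5% to 0.073/0.92 = 8% of the planned effect.

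**4. Power.** Noncentral t with 20 completers per arm, residual variance 1 − p(1 − p)ds² once site is in the model, and one further degree of freedom spent. Without site, power is 0.808. With site:

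| Smaller-site share | ds = 0 | ds = 0.2 | ds = 0.5 | ds = 0.8 |
|---|---|---|---|---|
| 12.5% | 0.807 | 0.809 | 0.818 | 0.835 |
| 25% | 0.807 | 0.810 | 0.826 | 0.854 |
| 50% | 0.807 | 0.811 | 0.832 | 0.870 |

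At ds = 0.5, leaving site out costs 1.0 to 2.4 points. At ds = 0, including it costs about 0.1 point.

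**5. Validity.** In simulation of minimization followed by ANCOVA at N = 48, the mean estimate was unbiased with and without site, and type I error was about 4 to 6% either way.

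**6. Degrees of freedom.** 48 × 0.8 = 38.4, so about 38 evaluable. Intercept, arm, gender and AKQ-C leave 38 − 4 = 34; adding site leaves 33.

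**The case against.** The strongest reply is that adjusting for the factors used in allocation is a coherent and valid analysis. Chance site imbalance is random error with mean zero, and the between-site variance left in the residual is what widens the interval to cover it. Lost precision and chance imbalance are therefore largely the same harm, and should not be counted twice. That stands.

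The design also makes a large site effect on change less likely. Baseline AKQ-C is a covariate, both arms are assessed in the same manner at each facility, testers are trained and blinded to arm, and ACAT therapists share training, a manual and one supervisor. This stands too, although none of it balances site, and blinding to arm does not remove differences between testers in different cities.

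A reader might infer something stronger: that the estimate is biased by site, or that badly lopsided splits are common. The documents do not support either. Over repeated randomizations the estimate is unbiased and the test holds its level. A 25-point imbalance arises in at most about 15% of trials under the assumed splits, and in about 2% if the smaller site has six participants. No site split or site effect is reported, so no actual distortion can be shown.

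**Conclusion.** The point holds as a minor one. Site is left out of both allocation and model in a two-city trial, and including it would be a nearly free improvement; the stated analysis is not wrong without it.

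Every size given rests on an assumed split (smaller site 6 to 24 of 48) and an assumed site difference. At 0.5 SD, the typical shift is about 0.05 to 0.07 SD, about 3 to 6% of the error variance is between sites, and up to about 2 points of power are lost. At 0.2 SD the power effect is well under half a point, and with no site difference the consequence is nil. Only at 0.8 SD does the power loss reach about 3 to 6 points. The planned sample size of 48 is unaffected.

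**What to change.** Leave the allocation as it is. With 41 of 48 already randomised, a change to the minimization could reach only the last seven participants. Add site as a fixed effect to the primary ANCOVA and to the secondary models that follow it, and record this before unblinded data are analysed. Two sites are too few for a useful random effect. Report allocation by site.

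The article schedules analysis from summer 2020 and was published in September 2020, so that point may have passed. If it has, keep the stated model as primary and report the site-adjusted model as a labelled sensitivity analysis, so that it is not read as a choice made after seeing the results.

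The cost is a sentence of plan wording and one residual degree of freedom (34 to 33 at 38 evaluable), which is about 0.1 point of power if the sites do not differ.
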